#### 3.2 Study Population

Adult ( $\geq 18$  year old) men from up to four candidate study communities will be enumerated and enrolled in the Aim 1 study if they meet eligibility criteria. In Aim 2, men and women who test HIV-positive will be enrolled in the treatment incentives trial. In the Aim 3 Pilot, men and women who are HIV-negative and considered at high-risk of HIV infection will be enrolled in the pilot trial. In the Aim 3 trial (following the Aim 3 Pilot), men and women ( $\geq 18$  years old and  $<60$  years of age) who are HIV-negative, recruited at high-risk venues in southwestern Uganda, and considered at high-risk of HIV infection will be enrolled. In our Aim 4 activities, we will conduct longitudinal follow-up of the HIV testing behavior of men enrolled in Aim 1.

### 4. Study Design

a. HIV Testing Incentives Trial (Aim 1): Randomized, controlled trial (RCT) of three types of incentive strategies (lottery-based, loss aversion-based, and fixed incentives) and multiple incentive amounts among adult male residents of rural Ugandan study communities. Eligible men will be randomized in an equal ratio to study groups.

b. HIV Treatment Incentives Trial (Aim 2): Randomized, controlled trial of a financial incentive strategy (with escalating incentive amounts for early treatment initiation and treatment maintenance vs. the no incentive standard of care) on the primary outcome of HIV virologic suppression (plasma HIV RNA  $<400$  copies/mL 6 months after randomization) among HIV-infected adult residents of rural Ugandan study communities. Eligible adults will be randomized in a 1:1 ratio.

c. Repeat HIV Testing Incentives (Aim 3 Pilot Trial): Randomized, controlled pilot trial of loss aversion vs. gain-framed incentive strategies vs. no incentive for the primary outcome of acceptability and feasibility of participation in a loss aversion strategy, to promote repeat HIV testing among HIV-negative, high-risk residents of rural Ugandan study communities. Eligible adults will be randomized to a control group, a gain-framed incentive group, or loss-aversion based group in a 1:1:3 ratio.

d. Repeat HIV Testing Incentives (Aim 3 Trial): Randomized, controlled trial of loss aversion (deposit contract) vs. gain-framed incentive strategies vs. no incentive (control) for the primary outcome of retesting for HIV 3- and 6-months following enrollment among HIV-negative, high-risk adults recruited from study sites in southwestern Uganda. Eligible adults will be randomized to the three groups (control, gain-framed and loss aversion incentive groups) in a 1:1:1 ratio.

e. Sustainability and Cost-Effectiveness (Aim 4):

- i. *Sustainability of incentives on HIV testing behavior*: Prospective study of HIV testing uptake at community HIV testing venues up to four years after HIV Testing Incentives RCT participants took part in the RCT.
- ii. *Cost-effectiveness*: We will measure the full resources and associated costs of implementing the incentive interventions for HIV testing using micro-costing (to quantify resources used and unit costs), and time and motion logs of study staff.

## 5. HIV Testing Incentives Trial

### 5.1 Recruitment & Enrollment of Study Participants

#### 5.1.1 Recruitment

Prior to the start of the study, study team members will meet with local officials and community representatives to discuss the study and plans for the enumeration of adult men. Using a map of the boundaries of the selected communities, study staff will systematically cover the entire area within the boundaries to identify and enumerate all households.

#### 5.1.2 Consent Process

An adult household member in each home will be visited during recruitment and will provide oral informed consent before information is collected on several variables about all household members, including the following:

- Name
- Relationship to head of household
- Contact information, including mobile phone number
- Demographic information such as age, gender, occupation and marital status.
- A fingerprint of each household member will be collected with the use of a fingerprint biometric device. (We have found this approach to be highly acceptable and had considerable success with in the ongoing SEARCH Trial in Kenya and Uganda)
- Social networks assessment
- The household's location will be recorded using hand-held GPS receivers.

#### 5.1.3 Screening for Enrollment

Following the census, study staff will review the eligibility criteria among household members and seek to recruit those who meet eligibility criteria (described below). Study staff will review the written informed consent form with eligible individuals and those who provide written consent to study enrollment will have the following performed:

- Baseline questionnaire
- Randomization to incentive strategy (Section 5.2 below)

We will attempt to enroll eligible individuals who are not available during the household visit by returning to the home at times when they are likely to be available.

##### 5.1.3.1 Inclusion Criteria

- (a) Male;
- (b) Aged  $\geq 18$  years;
- (c) Reside in one of the selected communities;
- (d) Consent to randomization to incentive strategy.

##### 5.1.3.2 Exclusion Criteria

- (a) Migration out of study community for  $\geq 6$  months per year in the year prior to enrollment.
- (b) Intention to move away from the community.

### 5.2 Randomization

We will compare two theoretically motivated incentive interventions to a standard, fixed incentive intervention. Each intervention will seek to encourage HTC uptake at testing venues in the community (described below).

The incentive interventions will have up to three different values in order to inform researchers and policymakers about the optimal incentive size. The *expected value* of each incentive intervention, within each tier of incentive value, will be the same so that we can draw unambiguous conclusions about the reasons why some incentive interventions work better than others. We will select up to three tiers of incentive value (e.g. low, medium and higher value incentive values), with the specific amounts of expected values per person in US dollars for the incentives determined during pre-enrollment community advisory board meetings. The expected value of the *highest* tier of incentive value will not exceed \$10/person, an amount that resembles

what has been used in some other studies in the region [27, 51], and that also corresponds to the sum of transport costs and the opportunity costs of time for some segments of the population.

Study participants will be randomized in equal ratios to the three incentive strategies and to up to three tiers of incentive value, as described below. Randomization will be performed with computer-generated assignments that are grouped in blocks so as to ensure roughly equal sizes in each study group.

### 5.3 Lottery-based Incentive Interventions

Study staff will inform men that if they come for an HIV test, they will be entered into a lottery that offers a chance to win high-value prizes. Staff will emphasize that *only those who come for HIV testing* will be entered into the lottery and that not everyone will win a prize. Participants will be informed at enrollment about the list of prizes and corresponding probabilities of winning them, in terms that are understandable to men with low numeracy (e.g., “1 in 20” rather than 5%). The probabilities of winning prizes will vary from about 1-5%, with higher value prizes having lower probability. Our pilot data from the SEARCH Trial indicate that lottery-based rewards are feasible and acceptable in communities.

Implementation: After HIV testing and counseling is complete, participants will be given a scratch card or sealed envelope that will reveal if they won a prize (we have used scratch cards in our studies in Kenya previously, and they are also widely used in Uganda). Prizes will be given to participants at the time their scratch card reveals they have won. The exact list of prizes will be determined after further consultation in study communities in year 1.

### 5.4 Loss Aversion-based Incentives

The prizes (i.e., incentives) given to participants in this arm will be worth approximately the same amount (in US dollars) as the fixed incentive (see below), and the expected value of a lottery prize (see above). At the time of randomization, study staff will either display a specific prize to the participant or will display multiple prizes to the participant and ask him to choose which one he would like to receive if he comes for HIV testing. Participants will be randomized to whether they see a specific prize or multiple prizes. The rationale for the latter strategy is that by actively choosing a prize, participants may form a greater attachment to it and may be more likely to come for HIV testing.

Staff will then spend the duration of the visit generating a sense of familiarity with the prize for the participant. Methods for generating a sense of familiarity will be developed based on experiences theorized to explain the emergence of psychological ownership [52], and after further pilot testing and consultation with community advisory boards in study communities in year 1. Staff will emphasize that men will not receive the prize if they do not participate in HIV testing and that their prize will be returned to them if they get tested. In this way, the incentive is framed as a loss rather than a gain, thereby leveraging loss aversion *while not requiring men in very low-income settings to experience an actual loss* [40, 42].

### 5.5 Fixed Incentive Interventions

Men will be informed that if they come for HIV testing, they will receive a specific prize (*gain framing*). The prize will be an item (such as a T-shirt) worth the same amount in US dollars as the loss aversion incentive (above), and the expected value of a lottery prize (above). The prize will be described verbally. This gain-framed incentive resembles the form that incentives usually take in most studies and will serve as a comparison to the lottery-based and loss-framed incentives described above.

In all study groups, men will be told about HIV testing venues where incentives will be provided, and encouraged to come for testing due to the various benefits of doing so, which include the availability of free ART, if eligible for ART by country-guidelines, at the local health center.

All participants will also receive text messages on a weekly basis that reminds them about the dates and locations of the HIV testing campaigns to be held in their community. Text messages will mention the incentives for testing that are specific to each participant. A sample of participants in the trial may also be selected at baseline or in subsequent years to low-cost interventions that facilitate planning for when they would like to come for an HIV test. Such planning prompts or “nudges” are intended to increase the likelihood of the desired behavior (HIV testing) at minimal expense without restricting participants’ individual autonomy to not go for an HIV test.

## 5.6 Outcomes Measurement

**Primary outcome: HIV testing uptake.** We will record whether each study participant tested for HIV at a study testing venue (see Section 5.6.1.1 below) within a period that is no longer than 12 months of randomization. We will use electronic fingerprint biometric measurements that link participants in real-time to a study ID at the time of HIV testing to determine whether study participants HIV tested or not (an approach that we have found to be highly acceptable and had considerable success with in the ongoing SEARCH Trial in Kenya and Uganda).

Secondary Outcomes:

**a) HIV test result** of each participant who gets tested.

**b) Risk preferences:** We will measure each participant's **risk preferences** at the time of enrollment using a standard approach developed by economists that we have piloted in Kenya previously [35]. Under this approach, a simple questionnaire is used to determine whether participants are risk seeking or risk averse when it comes to financial and non-financial decisions. This in turn can be useful for predicting whether they are likely to seek HTC and be influenced by the provision of certain types of incentives for HTC.

### 5.6.1 HIV Testing

#### 5.6.1.1 Testing Venues

We will measure HTC at one or more venues within each study community. These may include the community's government-run health facility (where there is likely to be a voluntary counselling and testing [VCT] clinic) or at mobile testing venues established by our study. HTC uptake will be recorded over a period of up to 12 months after enrollment and randomization. Mobile community-based testing venues are an established HTC strategy for increasing male testing, and we have piloted their use in rural Uganda [28, 53]. Other services offered at mobile HIV testing venues may include hypertension and diabetes screening, information and referral for medical male circumcision, instruction on condom use with distribution of free male condoms, men's health counseling, and other Uganda Ministry of Health approved health screening services such as tuberculosis or malaria screening for men with chronic cough or fever, respectively.

At the time they are enrolled in the study, all participants will receive information on when and where to find the testing venues where HTC uptake will be recorded.

#### 5.6.1.2 Testing Procedures

Pre-test counseling: Prior to undergoing diagnostic testing in the field laboratory, pre-test counseling will take place to inform and update participants on the diagnostic services offered and to answer questions.

HIV Testing: Rapid HIV Antibody testing for all participants will take place according to Uganda MoH policy and using the MoH HIV testing algorithm [54]:

1. Initial rapid HIV test
2. All negative results will be informed of their HIV-negative status
3. All positive results will be confirmed with a second rapid HIV test, performed either in series or in parallel with the first test.
4. Discordant results (first test positive, second test negative): participants with discordant rapid tests will undergo a third "tie- breaker" HIV rapid test. Participants with a positive "tie-breaker" test will be informed that they are HIV positive. Participants with a negative "tie-breaker" test will be told that their results are negative.

Non-HIV Health Services. The following services, delivered according to MoH guidelines (and many of which we have implemented in prior studies [28, 53] and the ongoing SEARCH Trial), may be offered at mobile HIV testing venues:

- *Recommended:* Finger-stick blood glucose measure
- *Recommended:* Syphilis screening (RPR)
- *Recommended:* Blood pressure measurement
- *Recommended:* HIV-infected participants: Point-of-care CD4 cell count testing
- *Recommended:* Malaria rapid diagnostic test (RDT) participants with objective fever ( $\geq 38.5$  degrees Celsius)

- *Recommended:* TB screening (sputum collection for microscopy, *Mycobacterium tuberculosis* culture, or other Uganda MoH approved sputum tests) for men reporting cough for >2 weeks.

**Post-test Counseling:** All participants, regardless of test results, will receive post-test counseling. Any cases of severe illness identified at a mobile testing venue will be offered transportation to the nearest in-patient health center for hospital-based treatment.

### 5.6.1.3 Biohazard Containment, Infection Control and Safety

The following procedures and precautions will be instituted throughout the HIV testing activities:

- Universal precautions during blood sticks
- Sharps containers for all lancets used for finger-sticks
- Biohazard trash cans in the van

### 5.6.2 Qualitative Measurements

**In-depth semi-structured interviews:** Upon completing measures of HTC uptake, we will recruit men who did and did not HIV test from each study group for in-depth semi-structured interviews in order to better understand: **a)** the *mechanisms* through which the incentives succeeded or failed; and **b)** the *characteristics* of men who do and do not respond to incentives. In accordance with principles of Grounded Theory [55], we will iteratively collect and rapidly analyze interview transcript data, continuing to randomly select participants within theoretically-informed categories (e.g. not only study group but categories such as age group or marital status) until the data attain theoretical saturation. Based on our prior qualitative research in the setting, we anticipate that each study group data will attain saturation with N=10-20 men who opted to test, and N=10-20 men who did not (N=about 100 total). The interview guide will be designed to elicit responses to two thematic areas: i) *men's perceptions, attitudes, and preferences related to the incentives offered*; and ii) *men's other motivations and barriers related to testing*, including qualitative exploration of risk preferences, other psychosocial factors (e.g. fatalism, avoidant coping style, internalized stigma, and perceived masculine gender norms counter to health-seeking behaviors) and contextual factors (e.g. livelihood strategies that interact with responses to incentives and testing). Trained interviewers will pursue lines of questioning following the domains of inquiry outlined above, while allowing participants to discuss salient subjects. Interviews will be audio-recorded, transcribed and translated into English.

## 5.7 Data & Statistical Considerations

### 5.7.1 Data Collection & Management

**Enumeration and baseline questionnaire data:** Staff will collect household enumeration and questionnaire data using hand-held computers (tablets). Before leaving the household, the completed enumeration lists and questionnaires will be checked for mistakes and completeness, ensuring each household has a unique identifier. Data from these devices will be transferred via a secure electronic transfer to our data center facility in Kampala and stored on a secure server.

**Household GPS:** Each household location will be mapped using a hand-held GPS receiver. Readings will be taken from the door of the household, if possible, or from a point that is most representative of the household. The GPS coordinates for each household will also be recorded in the tablet computer at the time of administering the enumeration questionnaire. GPS data will be synchronized from the GPS to a Microsoft Access database daily and then transferred via a secure electronic transfer to the data center facility in Kampala and stored on a secure server.

**Digital fingerprint biometric:** A digital biometric identifier based on an electronic fingerprint of each household member will be captured in an electronic database on the hand-held computer and linked to the household member name. A portable fingerprint reader will be connected to the tablet computer via a USB port and the biometric identifier will be saved into the electronic database on the tablet. The database will be transferred via a secure electronic transfer to the data center facility in Kampala and stored on a secure server.

**HIV Test Results:** Staff working at the HTC venues will record all lab test results, including HIV antibody and CD4 T-cell count results, and HIV diagnosis status information under each participant's study identification

number (ID) in either paper lab logs, or handheld computers. Staff will also record non-HIV screening/test results under each participant's study ID in either paper lab logs or handheld computers. Data from these logs or devices will be transferred via a secure electronic transfer to our data center facility in Kampala and stored on a secure server.

Qualitative Data: Staff will record interviews on audio devices using study IDs (not participant names), and transcribed interviews and translations will be data entered into appropriate software on password-protected study computers. Data from interviews will be transferred via a secure electronic transfer to our data center facility in Kampala and stored on a secure server.

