### 5.7.2 Analysis

Primary analysis: We will compare HTC uptake between the study groups. We hypothesize that HTC uptake among men offered lottery and loss aversion incentives will be higher than uptake among men offered fixed incentives. We will test for significant differences in HTC uptake between the following groups using the 2-tailed  $\chi^2$  analysis or other appropriate statistical methods: a) lottery vs. fixed incentive; and b) loss aversion vs. fixed incentive. To further inform policies that use incentives to promote health behaviors, we will compare HTC uptake among those receiving lottery vs. loss aversion incentives. We also hypothesize that those offered larger incentives amounts will have higher HTC uptake.

Secondary analyses: (a) **HIV-infected men:** We will compare the proportion of HIV testers who are HIV-positive in each of the study groups using 2-tailed  $\chi^2$  tests or other appropriate statistical methods. Our hypothesis is that the lottery incentive arm will have a *larger* proportion of HIV-infected men than the other arms, on the basis that it will draw men who are less risk averse.

(b) **Risk preferences:** We will estimate logistic regression models, or other appropriate statistical models, with an interaction term between study group and the participant's risk preferences. Our hypothesis is that lottery-based incentives will be most effective for men with risk seeking preferences, while other incentives will be most effective for men with risk averse preferences.

Analysis of qualitative data: Translated data will be imported into a qualitative analysis software program, for textual analysis [56] guided by grounded theoretical approaches [55], in which research team members iteratively analyze transcripts and develop a common set of codes describing patterns observed in the data. New codes proposed by research team members will be vetted and defined in relation to existing codes. As new data are collected and reviewed, and data reach analytic saturation, the research team members will independently code the interviews and discuss data segments that are particularly rich or difficult to code. Team members will discuss and resolve divergent coding and interpretations of findings to ensure that codes are applied consistently. Analytical memos will extract and summarize findings following the domains of inquiry outlined above, in order to extract themes and central ideas that explain the meaning of the data.

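### Aim 1's primary uptake comparison commits to no baseline adjustment, although community, age, marital status, occupation and home location are recorded before randomisation: an optional gain in precision of unknown size

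*Protocol*

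**What the plan says.** - **Data held before randomisation.** The household census in protocol section 5.1.2 collects "Demographic information such as age, gender, occupation and marital status". Section 5.7.1 adds that "Each household location will be mapped using a hand-held GPS receiver". Community is known from the eligibility rule "Reside in one of the selected communities" (5.1.3.1).
- **Primary analysis (5.7.2).** "We will test for significant differences in HTC uptake between the following groups using the 2-tailed" chi-square "analysis or other appropriate statistical methods: a) lottery vs. fixed incentive; and b) loss aversion vs. fixed incentive". No covariate or stratum is named.
- **Where a model is named.** The Aim 1 secondary analysis on risk preferences reads "We will estimate logistic regression models, or other appropriate statistical models, with an interaction term between study group and the participant's risk preferences". In Aim 2, section 6.6.2 names a logistic regression adjusted for socio-economic status, also as a secondary analysis.
- **Randomisation (5.2).** Individual and in blocks. Stratification by community is not stated.
- **Sample size (5.7.3).** About 1,000 men per strategy and two-sided alpha 0.05. Power above 80% is claimed for 6 points over 30% and for 7 points over 40%, both on unadjusted proportions.

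**The concern.** The protocol's own reasoning suggests that some of these variables bear on who comes for a test. Section 1.2 lists transport first among the immediate costs of testing. Section 5.2 justifies the ceiling on incentive value as an amount that "corresponds to the sum of transport costs and the opportunity costs of time for some segments of the population". Section 5.6.2 plans to sample interviewees by "not only study group but categories such as age group or marital status". None of these factors is then named in the Aim 1 analysis.

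If they predict attendance, an adjusted estimate of the difference in uptake has a smaller standard error than the crude one, and no further men need be enrolled. Adjusting for community would also deal with chance imbalance across the up to four communities, which the stated randomisation does not control. The gain would be most useful in the 30% vs 36% scenario, where the power margin is narrow. The point concerns baseline variables only, not the randomised tiers of incentive value.

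**Working it through.** **1. The plan's own figures.** Inputs from section 5.7.3: n = 1,000 per arm, two-sided alpha 0.05 (z = 1.96), 30% vs 36% and 40% vs 47%. The formula is the two-proportion test with pooled variance under the null:

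power = Φ[(d − 1.96·SE0)/SE1], where SE0 = √(2·p̄(1−p̄)/n) and SE1 = √((p1(1−p1)+p2(1−p2))/n).

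- 30% vs 36%: p̄ = 0.33, SE0 = √(0.4422/1000) = 0.02103, SE1 = √(0.4404/1000) = 0.02099. Then (0.06 − 0.04122)/0.02099 = 0.895, so power is 81.5%.
- 40% vs 47%: p̄ = 0.435, SE0 = √(0.49155/1000) = 0.02217, SE1 = √(0.4891/1000) = 0.02212. Then (0.07 − 0.04346)/0.02212 = 1.200, so power is 88.5%.

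Both claims of more than 80% reproduce without adjustment. For 80% power, the first scenario needs 963 per arm (996 with continuity correction), a margin of 37 (or 4) men per arm. The second needs 787 (815 with continuity correction).

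**2. Effect of adjustment.** Let R² be the share of variance in uptake explained by the baseline variables. The documents give no value, so R² is an assumption and a range is shown. Approximation: effective n = 1000/(1 − R²), and the standard error is multiplied by √(1 − R²).

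| Assumed R² | Effective n per arm | SE multiplier | Power, 30% vs 36% | Power, 40% vs 47% |
|---|---|---|---|---|
| 0 | 1,000 | 1.000 | 81.5% | 88.5% |
| 0.01 | 1,010 | 0.995 | 81.8% | 88.8% |
| 0.02 | 1,020 | 0.990 | 82.2% | 89.1% |
| 0.05 | 1,053 | 0.975 | 83.4% | 90.0% |
| 0.10 | 1,111 | 0.949 | 85.3% | 91.5% |
| 0.15 | 1,176 | 0.922 | 87.2% | 92.9% |
| 0.20 | 1,250 | 0.894 | 89.1% | 94.2% |

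A simulation of a logistic outcome (4,000 trials per setting) agrees with the approximation. Power rose from 80.4% to 82.5% at R² 0.048, from 81.7% to 85.3% at 0.099, and from 80.7% to 86.9% at 0.157.

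**3. How large might R² be?** As an illustration, take community alone, with four equal communities and mean uptake 30%. Then R² = (variance of the community rates)/(0.30 × 0.70).

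- 25, 28, 32, 35%: 0.00145/0.21 = 0.007
- 20, 25, 35, 40%: 0.00625/0.21 = 0.03
- 10, 20, 40, 50%: 0.025/0.21 = 0.12

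These rates are invented to show the scale. The gain can be anything from negligible to moderate.

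**The case against.** A reader might infer that the protocol fixes a crude chi-square that ignores all the baseline data, and so throws away a known amount of precision. The text does not support that reading, for four reasons.

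- **The method is open.** The chi-square is followed by a clause allowing other suitable methods, so an adjusted model is compatible with 5.7.2 as written. The covariate set is commonly left to the statistical analysis plan, which is not shown.
- **The named test is sound.** An unadjusted comparison of individually randomised arms is valid and meets the stated power in both scenarios. The 30% rate is presented as a low case, and at 40% vs 47% power is already 88.5%.
- **The size is not established.** No association of age, occupation, community or distance with uptake is reported. The transport text justifies an incentive ceiling and the age and marital categories are for interview sampling. Neither measures prognostic strength.
- **Distance is ambiguous.** Section 5.6.1.1 allows one or more venues, possibly mobile, so distance to the nearest venue has no single meaning. Recorded GPS has field uses in any case, such as mapping households and return visits.

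All of this stands, and it reduces the point to an efficiency suggestion. It does not remove it. The open clause permits adjustment but does not commit to it, whereas elsewhere the authors name a model when they intend one. Deciding between crude and adjusted estimates in advance is better than leaving the choice open.

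**Conclusion.** The point holds as an optional improvement of low severity. Section 5.7.2 names only an unadjusted test for the Aim 1 primary contrasts and commits to no baseline adjustment, although suitable variables are held on the men before randomisation. There is no error of validity and no shortfall against the stated power.

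The size of the gain rests wholly on an assumed R². Over 0.01 to 0.20, power at 30% vs 36% moves from 81.5% to between 81.8% and 89.1%. At 0.05 it is 83.4%, a gain of about 2 points. At the low end the gain is under half a point. With about 1,000 men per arm and a handful of covariates, the risk of losing precision by adjusting is negligible.

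**What to change.** In section 5.7.2, make the primary estimate for lottery vs fixed and for loss aversion vs fixed a standardised (marginal) difference in uptake. Take it from a logistic model with strategy, community, age, marital status and occupation, and keep the two-tailed chi-square as a check. The quantity estimated remains the difference in uptake between arms.

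Add distance from home to venue only if it is defined from the venues announced to participants at enrolment, with a stated rule where there is more than one.

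The cost is wording and a few rules set before outcomes are examined: coding of occupation, handling of missing covariates (census items come from one adult reporting for the household), and the variance method for the standardised difference. No further men and no further participant data are needed. Venue coordinates are the one extra item, and only if distance is used.
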